**5.5 Compliance checking method**

The compliance will be measured monthly (together with the collection of the vaginal swabs and urine and faeces samples) by pill counts. In addition, vaginal and faecal cultures will be examined on the presence of lactobacilli, and urine concentrations of TMP-SMX and proanthocyanidins will be determined.

1. **Clinical and laboratory evaluations**
   1. **Clinical evaluations**

During the course of the study, a set of Case Report Forms (CRFs) is completed. At t= 0 (at inclusion) demographic data (age, place of residence [for example nursing home], sexual activity, relevant medical history and concomitant diseases, number of UTIs in the previous year, medication, known urinary tract abnormalities, urinary catheter use) will be collected by the study coordinator.

Each month thereafter, during the 15 months of follow up, a questionnaire is sent to the patient. On those questionnaires, other relevant parameters concerning possible adverse events (e.g., allergic reactions, skin rash, gastrointestinal disturbances), possible interactions with other medication, and the medical history (change of place of residence, new concomitant diseases, medication change, pregnancy, hospital admissions, invasive procedures, operations, urinary catheter placement or removal) during the follow-up will be noted.

Quality of life questionnaires (concerning the general well-being and related to the disease) will be administered at baseline and 6, 12 and 15 months post-randomization.

- 1. **Laboratory evaluations**

At t= 0 and monthly thereafter, during the one year intervention period and the three months follow-up after stopping the intervention, material for culture will be sent to the patients. Vaginal swabs as well as samples from urine and faeces have to taken each month. Urine samples and faecal samples will be quantitatively analysed for the presence and degree of antibiotic (TMP-SMX) resistant micro-organisms. In addition, the vaginal swabs (2x) will be examined on the presence of lactobacilli and to one of the Gram stained swabs a Nugent score will be given. The scoring system examines vaginal cells at random and applies a 0-3 score for normal (dominated by Gram-positive bacilli resembling lactobacilli), 4-6 for intermediate (lactobacilli present along with Gram-variable rods), and 7-10 for bacterial vaginosis (no lactobacilli seen and cells colonized by Gram-negative rods). Urine samples will be examined for the presence of proanthocyanidins.

All samples (urine, faeces and vaginal swabs) will be analysed in the microbiology laboratory of the University Hospital Maastricht. To prevent growth of uropathogens in urine samples during transportation, dipslides will be used: a dipslide will be dipped in a fresh voided urine sample according to the manufacturer’s instructions. Dipslide, vaginal swabs (in transport medium) and faecal samples (1-2 gram) will be sent to the microbiological laboratory in Maastricht. The antibiotic susceptibility of the isolated resistant micro-organisms in the urine and faecal samples will be determined as a microbroth or Agar dilution method according to the SWAB standard [seeResistentie surveillance standaard SWAB 1999]. All other infections during the intervention and the follow-up period will be registered. Only in case of a symptomatic UTI, the patient will be asked to send a urine-dipslide to the microbiological laboratory in Maastricht.

For details about specimen collection requirements and laboratory tests: see table 2.

| **Specimen Type** | **When** | **Determination** | **Test** | **(Interpretation of)**  **results** |
| --- | --- | --- | --- | --- |
| Urine | Baseline, each month during follow-up + in case of symptomatic UTI | - Culture (max. 2 m.o.)  - Concentration TMP-SMX  - Analysis TMP-SMX -resistant m.o.  - Concentration proanthocyanidins | Dipslide  Microbroth dilution | Positive: >/=10³ CFU/ml urine  R, S, MIC (criterions NCCLS) |
| Faecal sample | Baseline, each month during follow-up | - Concentration *E.coli*  - Analysis TMP-SMX -resistant m.o.  - Concentration total lactobacilli, *L.GR-1, L. RC-14* | Agar dilution  Quantative agar culture | CFU/gram  R, S, MIC (criterions NCCLS)  CFU/gram |
| Vaginal swab | Baseline, each month during follow-up | - Concentration  total lactobacilli, *L.GR-1, L. RC-14* | Quantative agar culture | CFU/ml |

Table 2, specimen collection requirement and laboratory tests. M.o = micro-organisms, TMP-SMX = trimethoprim-sulfamethoxazole, CFU = colony forming units, R = resistant, S = sensitive, MIC = minimum inhibitory concentration, *L.GR-1* = *Lactobacillus rhamnosus Gr-1, L. RC-14* = *Lactobacillus reutri RC-14.*

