**2.2 Study endpoints**

**2.2.1 Primary endpoints**

- the numbers of recurrences of symptomatic UTI

- time to first occurrence of antibiotic resistance in urine or

faeces

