### Based on an expected success rate in prevention of recurrent UTIs with TMP-SMX of 95% [2], measured success rates of 85% and 87% in the premenopausal women treated with cranberries [8], and postmenopausal women treated with lactobacilli [5], respectively, a type I error rate of 0.05 (alpha, one-sided) and a type II error rate of 0.20 (beta), 130 analysable women are needed for each of the four treatment arms.

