**8.2.2 Primary outcome**

Data will be analysed according to the intention to treat principle. In the two trials, the (cumulative) proportions of symptomatic UTIs at 12 months will be compared between the groups (non-inferiority part), and the time intervals to the first occurrence of faecal and urine antibiotic resistance will be compared between the two groups using standard survival time analysis techniques (resistance part).

- - 1. **Secondary outcome**

Data differences between the proportions showing adverse effects at 12 months will be analysed similarly as the primary ones, except the quality of life measures at 12 months, for which multivariable linear regression will be used. Since antibiotic resistance is a gradual phenomenon, a more refined analysis using ordinal logistic regression, will assess differences in proportions of patients at different concentrations of antibiotic resistance between the treatment groups. Other secondary analyses pertain to all microbiological outcomes at 15 months.

In both trials we will also separately analyse the patients with uncomplicated versus complicated UTIs.

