### Asymptomatic bacteriuria: Presence of at least 10e3 CFU/ml of one or two micro-organisms in a culture of a clean voided urine sample isolated from a patient without symptoms of a UTI.

### Symptomatic UTI: Presence of bacteriuria (10e3 CFU/ml of one or two micro-organisms) in combination with at least one of the following symptoms: dysuria, frequency, haematuria, lower abdominal pain, flank pain or unexplained fever.

Complicated UTI: UTI in all men, pregnant women, women with structural or functional abnormalities of the urinary tract, or who are immunocompromised (e.g. having diabetes) or use immunosuppressive drugs.

Uncomplicated UTI: UTI without characteristics of a complicated UTI.

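### The resistance primary endpoint does not exclude urine samples sent because of a symptomatic UTI, so the chances of detecting resistance rise with UTI frequency, which is expected to be higher in the non-antibiotic arms

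*Protocol*

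**What the plan says.** Protocol section 2.2.1 gives the second primary endpoint as "time to first occurrence of antibiotic resistance in urine or" faeces. Section 8.2.2 says that "the time intervals to the first occurrence of faecal and urine antibiotic resistance will be compared between the two groups" by standard survival methods. Neither section restricts the endpoint to scheduled samples.

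Section 6.2 describes monthly collection and then states: "Urine samples and faecal samples will be quantitatively analysed for the presence and degree of antibiotic (TMP-SMX) resistant micro-organisms". Later in the same section an extra sample is requested: "Only in case of a symptomatic UTI, the patient will be asked to send a urine-dipslide to the microbiological laboratory in Maastricht". Table 2 puts both kinds of urine in one row, timed "Baseline, each month during follow-up + in case of symptomatic UTI", and lists one set of determinations for that row, including the analysis of TMP-SMX-resistant organisms. The faecal row is timed "Baseline, each month during follow-up" and nothing more.

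Appendix I defines a symptomatic UTI as "Presence of bacteriuria (10e3 CFU/ml of one or two micro-organisms) in combination with at least one of the following symptoms". Section 8.1 plans on 95% success with TMP-SMX, 85% with cranberries and 87% with lactobacilli, and accepts a success rate 10 points lower without antibiotics.

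**The concern.** Time to first resistance depends on how often one looks as well as on how much resistance there is. Monthly sampling is the same in both arms. UTI-triggered sampling is not: its frequency is the trial's other primary outcome, and it arises after randomisation, so neither randomisation nor blinding balances it.

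A sample from a confirmed UTI also contains bacteria by definition, whereas a monthly urine sample from a woman without symptoms may grow nothing to test. The extra looks may therefore be more productive than the scheduled ones.

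The objective in section 2.1.1 is whether non-antibiotic prophylaxis reduces selection of resistant organisms. If UTI-triggered isolates count, the endpoint mixes selection with UTI frequency. With UTIs expected to be commoner in the non-antibiotic arms, their time to first resistance is shortened and a real advantage is partly hidden.

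**Working it through.** **Inputs from the protocol.** 30% v 15% resistance (8.1); 130 analysable women per arm (8.1); 95% v 85% or 87% UTI success (8.1); 2-3 UTIs per patient-year without prophylaxis and 0.1-0.2 with TMP-SMX (Rationale); 12 months of treatment with monthly samples.

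**The plan's own figure.** Section 8.1 states 78.8% power for 30% v 15% and gives no alpha for this part. The normal approximation for two proportions with n = 130 and an assumed two-sided 0.05 has:

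- se0 = sqrt(2 × 0.225 × 0.775 / 130) = 0.0518
- se1 = sqrt((0.30 × 0.70 + 0.15 × 0.85) / 130) = 0.0510

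With continuity correction, power = Φ((0.15 − 1/130 − 1.96 × 0.0518) / 0.0510) = 78.8%, which matches. Without it, power is 82.9%, the baseline used below.

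**Model.** Let r be the detection chance at one monthly look, set so that 12 looks give the planned figure:

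- r = 1 − 0.70^(1/12) = 0.0293 for 30%
- r = 1 − 0.85^(1/12) = 0.0135 for 15%

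Add k UTI-triggered looks per woman-year, each with detection chance m × r. Then cumulative detection = 1 − (1 − r)^12 × (1 − m r)^k.

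**UTI rates.** The planning success rates imply k = −ln(0.95) = 0.05 for TMP-SMX, −ln(0.85) = 0.16 for cranberries and −ln(0.87) = 0.14 for lactobacilli. The other scenarios take 0.15 per year on TMP-SMX (midpoint of 0.1-0.2) against an assumed 1 or 2 per year without antibiotics. The values of m are assumptions throughout.

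**Worked example** (0.15 v 1 per year, m = 3, true resistance 15% in both arms):

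- antibiotic arm: 1 − 0.85 × (1 − 0.0404)^0.15 = 15.5%
- non-antibiotic arm: 1 − 0.85 × (1 − 0.0404)^1 = 18.4%
- spurious gap: 2.9 points

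| UTIs per year, antibiotic v non-antibiotic | m | Gap if both truly 15% (points) | Observed contrast if truly 30% v 15% | Power |
|---|---|---|---|---|
| Scheduled samples only | – | 0 | 30.0 v 15.0 (15.0) | 82.9% |
| 0.05 v 0.16 (planning, 85%) | 1 | 0.1 | 30.1 v 15.2 (14.9) | 82% |
| 0.05 v 0.16 (planning, 85%) | 5 | 0.7 | 30.6 v 16.0 (14.6) | 80% |
| 0.15 v 1 (assumed) | 1 | 1.0 | 30.3 v 16.1 (14.2) | 78% |
| 0.15 v 1 (assumed) | 3 | 2.9 | 31.0 v 18.4 (12.5) | 65% |
| 0.15 v 2 (assumed) | 1 | 2.1 | 30.3 v 17.3 (13.0) | 70% |
| 0.15 v 2 (assumed) | 3 | 6.2 | 31.0 v 21.7 (9.2) | 39% |

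With 87% in place of 85%, the gap is 0.1-0.5 points and power 81-82% over m = 1 to 5. The m ranges differ by row: m = 5 at the two assumed rates would give gaps of 4.8 and 10.2 points and power of 52% and 17%, but that combines a high rate and a high m, neither of which the protocol supplies.

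**The case against.** **The protocol never says in words that UTI samples count.** This is true. The sentence on resistance testing follows the one on monthly sampling, and the sentence on the UTI dipslide does not mention resistance. The urine row also lists TMP-SMX and proanthocyanidin concentrations, which section 5.5 treats as monthly compliance checks, so the row may be only a laboratory schedule. A reader should therefore not infer that the protocol expressly counts these samples. But an unrestricted endpoint in urine, together with a table row that tests both kinds of urine for resistance, does not exclude them. Which specimens make a primary event is part of the endpoint's definition, not mere analysis detail.

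**The size is easily overstated.** A reader might take UTI samples alone, assume 20% resistance per isolate and use 1 − exp(−rate × 0.20). That gives 3.0% at 0.15 UTIs per year and 39.3% at 2.5, a gap of about 36 points. The documents do not support it: it ignores the 12 scheduled looks and pairs TMP-SMX with no protection at all. At the planning rates the same formula gives 1.0% v 2.7-3.2%, about 2 points. The protocol also describes UTIs as ascending from colonising bacteria and some recurrences as relapses with the same isolate, so monthly samples may already have caught many resistant strains. This overlap would lower the table's figures too.

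**A UTI dipslide is not certain to grow an organism.** Agreed: bacteriuria is part of the UTI definition, and a woman with symptoms may send a negative slide. This is why m is varied from 1 upwards.

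**The expected direction is conservative.** This stands. It lessens the seriousness, but loss of power matters for an endpoint planned at 78.8%.

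**Conclusion.** The point holds as an endpoint definition that leaves ascertainment open to differ by arm. At the protocol's own planning rates the effect is negligible: 0.1-0.7 points of spurious gap and at most about 3 points of power. It becomes material only if UTI rates diverge more than planned: about 1-3 points and 65-78% power at 0.15 v 1 UTI per year, and about 2-6 points and 39-70% at 0.15 v 2. Those rates are assumptions, though not remote in women who enter with at least three UTIs in the past year and for whom the protocol cites 2-3 episodes per year without prophylaxis.

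The figures rest on independent looks, a constant detection chance, 12 monthly looks, m of 1 to 5 (planning rates) or 1 to 3 (assumed rates), and a comparison of proportions rather than a survival test.

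A reader might infer a risk of a falsely favourable resistance result. The documents point the other way, and that would need UTI rates opposite to those planned. Nor does this point show the stated power or sample size to be wrong.

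**What to change.** In sections 2.2.1 and 8.2.2, state that the primary resistance endpoint counts only the scheduled monthly urine and faecal samples. Report resistance among symptomatic-UTI isolates as a separate secondary outcome, and add a sensitivity analysis of the primary endpoint that includes them. Label Table 2 to match.

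Urine should stay in the primary endpoint. Making faeces the sole primary specimen would rewrite the objective in section 2.1.1, which names both, and is not needed to remove the problem.

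The cost is wording: no sample or visit is added and no data are lost. The downside is slightly fewer primary resistance events. Resistant symptomatic UTIs, which are clinically relevant in themselves, are still reported as their own outcome.

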**7 Safety**

**7.1 Adverse event**

As described above, all patients will be checked for contra-indications (including renal and liver failure) and relevant interactions for or with the drugs used in this study. Patients with contra-indications for or relevant interactions with study medication will be excluded from the study.

Most reported adverse events from the used antibiotics are: gastro-intestinal disturbances, vaginal symptoms (rash or itching) and allergic skin reactions. Because of the low prescribed dosage of antibiotics, and frequent evaluations, major adverse events are expected to occur very rarely and will be detected early.

The safety of cranberries is considered to be excellent. Some patients may experience a slight laxative effect, depending on the amount ingested (19). Nevertheless, at least one author warned that ingesting a large amount of cranberries over a longer period of time may increase risk of some types of urinary stones in high-risk patients because of the increased urinary excretion of oxalate and slight urinary acidification (20). There are also reported several cases about the possible interaction between cranberries and warfarin (21). For those reasons patients with a history of nephrolithiasis or those who use oral anticoagulants are excluded from RCT-A.

In the few studies using *Lactobacillus rhamnosus GR-1* and *L. reuteri RC-14* no adverse events were reported after oral intake (12).

An adverse event (AE) is defined as any health-related reaction, effect, toxicity or abnormal laboratory result that a participant experiences during the course of a study irrespective of relationship to study treatment. This includes changes in a participant's condition or laboratory results which have or could have a deleterious effect on a participant's health or well-being.

A serious adverse event is defined as any experience that is fatal or life-threatening, permanently disabling, requires in-patient hospitalization, or is otherwise judged to be serious by the study coordinator.

**7.2 Stopping rules**

The study drug may be withheld or discontinued permanently if the AE is thought to be possibly related to the study drug, as judged by the patient’s general practitioner or the study coordinator.

- 1. **Annual safety rapport**

Each year an annual safety rapport will be written. This is a safety report taking into account all new safety information received during the reporting time. This report will be examined by a group of independent medical specialists.

**8 Statistical analysis**

**8.1 Power and sample size calculations**

### Non-inferiority part: It is known from clinical practice that many women are afraid of contracting resistant bacteria. For that reason they do not want to take antibiotic prophylaxis over an extended period of time. These women are even willing to take non-antimicrobial prophylaxis with a lower success rate in preventing UTIs compared to antimicrobial prophylaxis. Therefore, we accept a 10 percent lower success rate of the non-antibiotic compared to the antibiotic prophylaxis.

### Based on an expected success rate in prevention of recurrent UTIs with TMP-SMX of 95% [2], measured success rates of 85% and 87% in the premenopausal women treated with cranberries [8], and postmenopausal women treated with lactobacilli [5], respectively, a type I error rate of 0.05 (alpha, one-sided) and a type II error rate of 0.20 (beta), 130 analysable women are needed for each of the four treatment arms.

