**Appendix I : List of definitions 29**

**1 Introduction**

- 1. **Background**

Urinary tract infections (UTIs) occur frequently. The incidence of UTIs in a Dutch family doctor’s practice is about 30 to 40 per 1000 patients per year. Eighty to ninety percent of UTIs affect women (1). One in three women will have at least one UTI by the age of 24 years, and 40-50% of women will experience at least one UTI during their lifetime. The frequency of UTIs increases with age while, for example, patients with a urinary catheter, diabetes mellitus, spinal cord lesions, or a neurogenic bladder are particularly susceptible (2). Due to the increasing life expectancy and the increasing number of patients suffering from diabetes, it is to be expected that the prevalence of UTIs will rise (3).

In addition to the impact on quality of life, UTIs have financial implications (3;4). Although the costs associated with a single episode of UTI are relatively low, due to the high incidence total costs are estimated to be around 100 to 300 million Euro per year in the Netherlands (5).

It is of note that 20 to 30 percent of the women experiencing an episode of UTI will experience recurrent UTIs. Recurrent UTIs (RUTIs) are usually defined as at least three episodes of UTI in the previous twelve months or two episodes in the previous six months(6). RUTIs can be based on a “relapse” after treatment cessation with the pre-therapy isolate or as a “reinfection” with a different organism after initial treatment cessation (2). Long-term low-dose antibiotic prophylaxis can be recommended for prevention of reinfections in women with UTIs (7).

- 1. **Rationale**

Randomized trials (RCTs) have documented that continuous prophylaxis with trimethoprim-sulfamethoxazole (TMP-SMX) diminishes recurrences by 95 percent (from 2 to 3 episodes per patient-year to 1 or 2 episodes per 10 patient-years) (8). However, these successes may not last another decade now that antibiotic resistance is increasingly becoming a problem. The most important risk factor for having a UTI resistant to TMP-SMX is its recent or present use (9). During a 2-week follow-up study in healthy students, who took TMP or TMP-SMX prophylaxis, a total number of 82 out of 86 students developed resistant micro-organisms in their faeces (10).

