### UTIs result almost exclusively from the ascending route. Bacteria colonizing the perineum and vagina can enter the urethra and further ascend to the bladder or even the kidneys. The colonization can be inhibited by the normal vaginal flora: lactobacilli*,* which produce lactic acid, and maintain a low vaginal pH that inhibits the growth of many uropathogens. In postmenopausal women lactobacilli disappear. This results in a higher chance of colonization of the vagina with *Enterobacteriaceae*. It has been demonstrated that vaginal colonization with *Escherichia coli* and the absence or low levels of vaginal lactobacilli were independently associated with a history of a recent UTI (11). It has also been shown that oral administration of *Lactobacillus rhamnosus GR-1* and *L. reuteri RC-14* restores normal vaginal lactobacilli flora and reduces colonization by potential pathogenic bacteria (12). In a RCT with postmenopausal women with a history of recurrent UTIs, the incidence of UTIs was reduced in the estriol treated group compared to the placebo group (0.5 *versus* 5.9 episodes per patient year; p<0.001). More specifically, the topical application of vaginal estriol cream in the treatment group led to re-colonization of the vagina by lactobacilli in 23 of the 36 women. There was a strong positive relation between vaginal colonization status and the risk of infection: No UTIs developed in 20 of the 23 women who were colonized with lactobacilli (success rate of 87 percent) compared with 6 out of the 13 (success rate 46%; difference 41 (95%CI from 10 to 71) who were not colonized with lactobacilli (13).

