### The adherence of uropathogens to the bladder mucosa is another essential step in the pathogenesis of UTIs. In that process, adhesins (fimbriae) are important virulence factors. Although virulence factors have been characterized best in *Escherichia coli* (the most prevalent uropathogen) many of the same principles are applicable to other Gram-negative uropathogens. Cranberries contain fructose and proanthocyanidine, which inhibit the adherence of type 1 fimbriae of *E. coli* (the most important virulence factor in cystitis) and the expression of P fimbriae (the most important virulence factor in pyelonephritis), respectively (14;15). In a RCT with pre-menopausal women, the incidence of UTIs in the cranberry-treated women was only 16% (versus 36% in the control group; difference 20%; 95%CI from 3% to 36%; p=0.023), during a 6 months follow-up (16). Furthermore, it has been demonstrated that cranberry juice may also offer protection against resistant strains of *E. coli* by a mechanism that is not likely to increase selective pressure associated with antibiotic resistance (17).

- 1. **Purpose**

To quantify the effect of antibiotic prophylaxis compared to two non-antibiotic prophylaxis modalities on the incidence of symptomatic UTIs in pre- and post-menopausal women with recurrent UTIs. In addition, we assess differences in the development of bacterial drug resistance.

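### The success rates in section 8.1 (95%, 85%, 87%) are not 12-month UTI-free proportions under the study regimens, and the stated 80% non-inferiority power does not hold even at face value

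*Protocol*

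**What the plan says.** Section 8.1 sets the margin: "we accept a 10 percent lower success rate of the non-antibiotic compared to the antibiotic prophylaxis". It then takes an "expected success rate in prevention of recurrent UTIs with TMP-SMX of 95% [2], measured success rates of 85% and 87" percent; in full, the two alternatives are given as "measured success rates of 85% and 87% in the premenopausal women treated with cranberries [8], and postmenopausal women treated with lactobacilli [5], respectively". With "a type I error rate of 0.05 (alpha, one-sided) and a type II error rate of 0.20 (beta") it arrives at 130 analysable women in each of four arms. Section 8.2.2 makes the non-inferiority comparison one of (cumulative) proportions with symptomatic UTI at 12 months.

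The Rationale in section 1 is where these figures can be traced:

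- TMP-SMX prophylaxis "diminishes recurrences by 95 percent (from 2 to 3 episodes per patient-year to 1 or 2 episodes per 10 patient-years").
- In the cranberry trial "the incidence of UTIs in the cranberry-treated women was only 16% (versus 36% in the control group"), over 6 months of follow-up.
- In the treated arm of a vaginal estriol trial, 23 of 36 women were recolonised, and "No UTIs developed in 20 of the 23 women who were colonized with lactobacilli (success rate of 87 percent"); among the other 13, 6 stayed free of UTI.

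**The concern.** The three rates are subtracted from one another as if they were the same quantity, but they differ in metric (rate reduction or proportion), horizon (6 months, 12 months or unstated) and treatment (estriol cream standing in for oral lactobacilli). Section 8.1 calls the 87% measured in women treated with lactobacilli, which the Rationale contradicts. The bracketed sources do not help: in the reference list, 2 is an epidemiology review, 8 is the review that the Rationale cites for TMP-SMX, and 5 is a national health report. None is the cranberry trial (16) or the estriol trial (13).

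At stake is the sample-size rationale of both trials. If true 12-month event risks are higher than 5 to 15%, the variance rises. If the expected deficit is at or near the margin, non-inferiority is unlikely to be shown even when the planning assumptions are correct.

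**Working it through.** **1. The plan's own figure.** Inputs from 8.1: 0.95 and 0.85, one-sided alpha 0.05, power 0.80. For a test of difference,

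n = [1.645·√(2·p̄·q̄) + 0.842·√(p₁q₁ + p₂q₂)]² / d²

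With p̄ = 0.90 and d = 0.10, this is (1.645 × 0.4243 + 0.842 × 0.4183)² / 0.01 = 110.2, or 111. The continuity correction n/4·[1 + √(1 + 4/(n·d))]² gives 129.5, or 130. So 130 is reproduced, as a difference test. The same test for 0.95 against 0.87 gives 158, or 182 with the correction.

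**2. The same inputs as a non-inferiority test.** The margin M is read as 10 absolute points.

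n = (1.645 + 0.842)²·(p₁q₁ + p₂q₂) / (M − d)²

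- 0.95 against 0.85: M − d = 0, so no n suffices.
- 0.95 against 0.87: 6.18 × 0.1606 / 0.02² gives 2,483 per arm.

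Power at 130 per arm = Φ[(M − d)/SE − 1.645], with SE = √[(p₁q₁ + p₂q₂)/130].

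- 0.95 against 0.85: Φ(0 − 1.645) = 5%.
- 0.95 against 0.87: SE = 0.0351; Φ(0.57 − 1.645) = 14%.

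**3. What the sources imply at 12 months.** The assumptions are Poisson episodes on TMP-SMX and a constant cranberry hazard.

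- TMP-SMX, 0.1 to 0.2 episodes per patient-year: exp(−0.1) = 90.5%, exp(−0.2) = 81.9% UTI-free.
- Cranberry, 84% UTI-free at 6 months: 0.84² = 70.6%.
- 87%: 20/23. The whole estriol arm is (20 + 6)/36 = 72%, with follow-up length not stated.

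**4. RCT-A on a common scale**

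| Case | TMP-SMX | Cranberry | Deficit (points) | Power at 130 per arm |
|---|---|---|---|---|
| 12 months, 0.1 per year | 90.5% | 70.6% | 19.9 | 0.01% |
| 12 months, 0.2 per year | 81.9% | 70.6% | 11.3 | 2.9% |
| 12 months, 15% in place of 16% | 81.9–90.5% | 0.85² = 72.3% | 9.6–18.2 | 5.8% to 0.03% |
| 6 months, no cranberry extrapolation | 90.5–95.1% | 84% | 6.5–11.1 | 21% to 2.6% |

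Example, second row: SE = √[(0.819 × 0.181 + 0.706 × 0.294)/130] = 0.0523; (0.10 − 0.113)/0.0523 = −0.25; Φ(−0.25 − 1.645) = 2.9%.

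Allowing gamma-distributed differences between women (variance 0.25 to 5) leaves the 12-month deficit at 10.4 to 19.5 points.

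**5. Equal arms.** If the true proportions are the same, d = 0. At 81.9% SE = 0.0478 and power is 67%; at 90.5% SE = 0.0364 and power is 86%.

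**The case against.** A reader might infer that the protocol's own figures prove the RCT-A deficit to be larger than the margin. They do not. That reading needs Poisson episodes, a constant cranberry hazard in months 6 to 12, for which the protocol gives no data, and comparability of two separate studies. At 0.2 episodes per year the deficit falls to 10 points if the second-half cranberry hazard is 0.89 times the first-half hazard; at 0.1 per year it would have to fall to 0.25 times. The 6-month comparison straddles the margin. This objection stands, so the 11 to 20 points are conditional.

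A reader might likewise put the 72% of the whole estriol arm into RCT-B and read off a low power. The documents do not support this. The treatment is estriol cream, not oral lactobacilli, and the horizon is unstated. The same source's 0.5 episodes per patient-year would give exp(−0.5) = 61% under the Poisson conversion, not 72%. The low-end deficit, 81.9 − 72.2 = 9.7 points, is inside the margin. The 72% shows only that 87% is a selected subgroup.

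Two smaller points also stand. The link from 85% to the 16% risk is an inference, since 16% implies 84% and the citation does not match, although it is the only cranberry result that the protocol reports. And the protocol does not define success explicitly; UTI-free at 12 months is the natural reading of 8.2.2, whereas section 2.2.1 names numbers of recurrences.

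Finally, 8.1 calls the TMP-SMX rate expected, and planning values may be uncertain. That does not cover describing the 87% as measured on lactobacilli, nor the face-value result in step 2.

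**Conclusion.** Wrong as written. Without any modelling, the 87% is misattributed, the 95% matches a rate reduction and not a proportion of women, the citations do not lead to the sources, and the stated inputs give non-inferiority power of 5% (RCT-A) and 14% (RCT-B) at 130 per arm where 80% is claimed. This rests only on reading the margin as 10 absolute points and on the normal approximation.

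The size of the true RCT-A deficit is less certain: about 11 to 20 points (power 3% or less) with Poisson episodes and a constant hazard, about 10 to 18 if the 6-month risk is 15%, and about 6.5 to 11 on a 6-month scale. No expected deficit can be derived for RCT-B. Even with truly equal arms at 82 to 90% UTI-free, power is about 67 to 86%, so 80% is reached over only part of the most favourable range.

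**What to change.** In section 8.1:

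- Replace the three rates with assumed 12-month UTI-free proportions on one scale, as ranges, and state the conversion assumptions. The 71% for cranberry should appear as one value within a range, not as the new planning figure.
- Label the cranberry and lactobacilli values as assumptions, and delete the statement that 87% was measured in women treated with lactobacilli.
- Restate power at 130 per arm with a non-inferiority formula over those ranges, including the equal-arms case (about 67 to 86%), so that assumptions, margin and formula are consistent with each other.
- Correct the bracketed citations to match the reference list.

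The cost is a rewrite of one section, with no extra patients. The downside is that the stated power becomes less favourable.
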